**5**. **Goal of the study**

The goal of this research is to improve the tuberculosis control programme of Ethiopia

**5.1. General objective of the study**

To improve interventions to carry out community based tuberculosis control programme in southern Ethiopia.

**5.2. Specific Objectives:**

1. To evaluate the diagnostic value and applicability of community based tuberculosis screening tool in tuberculosis case detection,
2. To estimate the treatment outcome of tuberculosis patients supervised by community health agents or tuberculosis treatment supervisors
3. To find out the costs per tuberculosis patient treated successfully
4. To find out the acceptability of community based directly observed short course therapy
5. To find out the proportion of tuberculosis patients infected by human immunodeficiency virus

**Table** - **Summary of the individual studies**

| **Paper** | **Objectives** | **Study design** | **Study population** | **Duration** |
| --- | --- | --- | --- | --- |
| I. | To evaluate the diagnostic value and applicability of community based tuberculosis screening tool in tuberculosis case detection | Cross-sectional study | TB suspects older than 15 years old | Sep 2006/ Mar 2008 |
| II. | To estimate the treatment outcome of tuberculosis patients supervised by community health agents or tuberculosis treatment supervisors | Randomized control community trial | TB patients | Sep 2006/ Mar 2008 |
| III. | To find out the costs per tuberculosis patient treated successfully | Randomized control community trial | Health workers and TB patients | Sep 2006/ Mar 2008 |
| IV. | To find out the acceptability of community based directly observed short course therapy | Cross-sectional study | Health workers and TB patients | Mar 2007/ Mar 2008 |
| V. | To find out the proportion of tuberculosis patients infected human immunodeficiency virus | Cross-sectional study/survey | TB patients older than 15 years old | May 2006/ Oct 2006 |

**The research project in relation to the public health model of tuberculosis control**

Non infected

TB infected

Disease development

Recognition of symptoms

Health care seeking

Getting diagnosis

Treatment compliance

Treatment outcome

Study III - Cost per TB

patient treated successfully

Study I - diagnostic value and applicability of TB symptom score

Study II - estimate treatment outcome of TB patients

Study IV - acceptability of community based

tuberculosis care

**Post TB social consequences**

Study V - estimate the proportion of tuberculosis patients infected with HIV

**6.** **Methods**

**6.1. Study area and population**

Southern region is the third large stand populous regions in Ethiopia. It is located in the southwest part of the country with a population of 14.08 million. It has thirteen zones and eight special districts. The health service coverage is 50 %. However, the user rate is only 32 %. Tuberculosis diagnostic facilities are only located in health centres and less accessible to the patients.

Sidama zone is in southern region of Ethiopia. It has 10 districts and 2 city administrations. It is one of the most densely populated areas of the region with a population of about 2.8 million. It has one hospital, 20 health centres, 26 health stations and 85 health posts. The health service coverage is 55%.

In 1996, the DOTS started in Sidama. Currently all health facilities except all health posts deliver DOTS. The zone reports many tuberculosis cases. In addition, there are many community health workers in the zone. Some of these are community based reproductive health agents, traditional birth attendants, community health promoters, health extension workers and others. Practically so far, they have not participated in tuberculosis control programme.

**6.2.** **Study design**

**Study - I**

This is a cross-sectional study to evaluate the diagnostic value and applicability of community based tuberculosis-screening tool in tuberculosis case finding. The investigator will select matched clusters and randomly allocate to intervention and non-intervention clusters. Community health agents from the intervention clusters will organize community mobilization sessions monthly and register patients with cough of two weeks or more. Then they will run the diagnostic tool. Patients with symptoms suggestive of pulmonary tuberculosis will give sputum specimen according to the recommendation of national tuberculosis guideline. The community health agent will keep the sputum specimen in a box prepared for this purpose and transport the sputum specimen, the same day, to diagnostic health institution for laboratory examination. Laboratory technicians will stain the sputum specimen using by Ziehl-Neelsen technique on the same day. Then they will do direct microscopic examination. They will make the results ready for the next day. In addition, they will send sputum specimen for fluorescent microscopy, bleach digestion technique and culture. Patients in the non-intervention clusters will continue the conventional self-reporting and investigation in diagnostic health facilities.

**Study - II**

This is a randomized controlled community trial to estimate the treatment outcome of tuberculosis patients treated by community based directly observed short course therapy. The investigator will select clusters and match for tuberculosis treatment outcome. Then will randomly allocate them to intervention and control clusters. Health workers and community health agents in the intervention clusters will receive training on community-based tuberculosis care and its implementation. They will also discuss with diagnosed tuberculosis patients about the disease and selection of treatment supervisor. Tuberculosis patients will select tuberculosis treatment supervisor from their area and discuss with health worker about their role and responsibility. Once agreed up on, tuberculosis patients will start supervised short course therapy in their community under tuberculosis treatment supervisor. The study will follow the national tuberculosis programme guideline for patient diagnosis, treatment, follow-up, recording and reporting. Patients in the non-intervention clusters will continue conventional health-facility based directly observed short course therapy.

**Study - III**

This is a randomized controlled community trial to find out the cost per tuberculosis patient treated successfully. The study follows societal perspective of cost analysis. The main cost items related to the costs of tuberculosis prevention and control programme will be collected as for diagnosis, follow up and supervision including patient and community health workers time and costs. Data collectors will also get records from district finance offices. The data collectors will calculate cost of time based on monthly salary of health workers and tuberculosis patients if they are in the productive age groups. In addition, the cost of the person accompanying the patient will be included. The outcome indicator for the study is the cost per patient treated successfully.

**Study - IV**

This is a cross-sectional study to find the acceptability of community based tuberculosis care by health workers, community members, and tuberculosis patients. Health workers, tuberculosis patients and community members will participate in the study districts. The data collectors will randomly select tuberculosis patients, health workers, health extension workers, tuberculosis treatment supervisors and community health agents who are directly involved in tuberculosis patient care. From the community previously treated tuberculosis patients and community members living closer to tuberculosis patients, next fifth household heads will be taken. Trained data collectors will administer a pretested questionnaire about the acceptability of community-based TB care.

**Study - V**

This is a cross-sectional study or survey to find the proportion of tuberculosis patients infected with human immunodeficiency virus. The investigator will select ten sites from the region as part of regional surveillance of HIV infection among tuberculosis patients. The study will include all tuberculosis patients diagnosed over six months period. Trained laboratory technicians and health workers from tuberculosis clinic /data collectors/ will administer pr-tested questionnaire and record socio-demographic variables as age, sex, residence, classification and category of tuberculosis. Tuberculosis patients will give serum for HIV testing. The laboratory technicians will label and store the blood specimen as per the recommendation for HIV testing. They will transport the specimen to regional reference laboratory under cold chain. Trained laboratory technologists in the regional reference laboratory will do HIV testing under national testing algorithm. The results will be anonymous and unlinked.

## 6.3. Permission to continue

The investigator will discuss with the national tuberculosis prevention and control programme about the procedure and all the supplies needed as drugs, reagents, sputum cups, and formats. In addition, the investigator will discuss with authorities and tuberculosis programme coordinators at all levels the regional health bureau, zonal, district, health institutions and the community leaders the aim and the implementation of the intervention study.

**6.4. Ethical clearance**

The investigator will get ethical clearance from University of Bergen and Southern Nations, Nationalities and Peoples Regional Health Bureau Ethical Review Committee.

**6.5. Data collection and handling**

In collaboration with programme coordinators, the investigator will train health workers and community health agents according to the training guideline. Except for those specifically prepared for the study, will use formats used by the national tuberculosis control programme formats. Training of data collectors will focus on community-based tuberculosis care activities, individual studies, data collection techniques and administering a questionnaire. The training will have practical pretesting session. Data collectors will receive field guides and checklists prepared as a reference for the study period.

Health workers and community health agents will give questionnaires completed to the investigator or supervisors. The supervisors will check the completeness and accuracy of the questionnaires. The investigator will file and keep the filled questionnaires.

**6.6. Quality assurance**

Community health agents will be trained about community based tuberculosis care, identifying tuberculosis suspects, sputum collection and handling, recording and reporting, selection of tuberculosis treatment supervisor, and drug and supply management. The data collectors will receive training materials, checklists and field guides for field activities.

The research project and the national tuberculosis control programme will work together during the study period to help easy take over of the activity after the end of the study. Supervision schedule will be set in partnership with the follow-up plan of the health care system of the region except for specific supervision schedules for the intervention.

Tuberculosis programme coordinators will supervise tuberculosis treatment supervisors during follow-up. The programme coordinator and the investigator will supervise the health institutions. In addition, the investigator, zonal and regional tuberculosis programme coordinators, will supervise data collectors and treatment supervisors.

Field supervisors will contact tuberculosis patients, treatment supervisors, community members and health workers. In addition, they will cross-check five per cent of the data in the community with tuberculosis unit register in health institutions and woreda tuberculosis registers. The programme coordinator alone, or with the principal investigator will supervise the activities on weekly basis to provide supplies, do rapid assessment of the general activities and give timely solution to the problems met. Reference laboratory technologists will take five percent of tuberculosis slides done in health facilities for quality control. In addition, two independent technologists in the reference laboratory will check HIV test results.

**6.7. Analysis plan**

The investigator will check the data, sort and review it manually for errors and inconstancies. Then will use SPSS 13.1 for Windows for analysis.

# 7. Project management and work plan

The principal investigator, in teamwork with tuberculosis programme coordinators, local community leaders and community health workers, will oversee the tuberculosis control in the study areas. He will also take care of the administrative issues, overall help of the field activities and regular checking of the project progress. The principal investigator will keep proper records of the research and regularly communicate the progress and possible problems met with his supervisor.

**PART TWO INDIVIDUAL STUDIES**

**STUDY ONE - TO EVALUATE THE DIAGNOSTIC VALUE AND APPLICABILITY OF COMMUNITY BASED TUBERCULOSIS SCREENING TOOL IN TUBERCULOSIS CASE DETECTION**

**1. Objective**

- to evaluate the diagnostic value and applicability of community based tuberculosis screening tool in tuberculosis case detection

**2. Methods**

**2.1. Study design**

This is a cross-sectional study to evaluate the diagnostic value and applicability of community based tuberculosis-screening tool in tuberculosis case finding. The investigator will divide study sites into different clusters and match them based on the previous tuberculosis case finding and treatment outcome. He will pair the matched clusters. Then he will randomly allocate the paired clusters into intervention and control groups. This study will be carried out in intervention clusters parallel with the second study on treatment outcome. The study will include 15 years or more tuberculosis suspects who experienced productive cough of two or more weeks.

Trained community health workers will organize sessions of community mobilization on monthly basis. They will teach about tuberculosis its prevention and control. Community health workers will interview community members who have the symptoms suggestive of tuberculosis. Then they will run the diagnostic tool. All tuberculosis suspects who meet the criteria will give sputum specimen as per the national guideline recommendation. Community health workers will collect the sputum specimen label it and keep it in a box prepared to transport the specimen to diagnostic health facilities. Laboratory technicians will do direct sputum microscopic examination for acid-fast bacilli using Ziehl-Neelsen staining technique. The laboratory technicians will also send sputum specimen to Yirgalem hospital for culture, bleach digestion and fluorescent microscopy.

**2.2.** **Study variables**

The study variables are the socio-demographic characteristics as age, sex, education, marital status, tuberculosis symptoms, the duration and history related to tuberculosis.

**2.3. Data collection techniques and tools**

As part of tuberculosis prevention and control strategy, community health agents will be trained how to identify tuberculosis suspects from the community. They will also receive practical training about using the diagnostic tool, sputum collection, and coding, labelling, and handling technique. Tuberculosis programme will supply sputum cups and sputum collection boxes for community health agents. They will set up referral system among the health institutions, the laboratory technicians and community health agents. In addition, will set dates for sputum transporting, smear result, treatment and follow up of patients.

Community health workers will organize sessions of community mobilization every month. They will run the diagnostic tool. All tuberculosis suspects who meet the criteria will give sputum specimen for laboratory examination. Tuberculosis suspects will give sputum specimen as per the national guideline. They will give the first sputum specimen at spot after running the diagnostic tool. They will go home with the second labelled sputum cup and come next day with morning sputum. They will give the third sputum specimen when coming with the second next day. Community health workers will collect all sputum specimens, fill laboratory request formats, label sputum cups as per the national tuberculosis programme recommendation and keep it in a box prepared for sputum store in the community. Community health workers will transport the sputum specimen and deliver it to the laboratory technicians in the diagnostic health institution.

The laboratory technicians will do three direct sputum microscopy examinations by using Ziehl-Neelsen technique on the same day when they received sputum specimen. They will make the results ready for the next day. In addition, laboratory technicians will send the sputum specimens to Yirgalem hospital for culture, bleach digestion technique and fluorescent microscopy. We will use Lowenstein-Jenson medium under standard culture requirement to grow mycobacterium tuberculosis. Two independent trained laboratory technicians will do the microscopic examinations. The laboratory technicians will send a signed result to third independent record keeper. The investigator will check the results and report those patients who turned out to be smear positive for tuberculosis. Health workers will start them on antituberculosis treatment as per the national tuberculosis manual.

Laboratory technicians in the diagnostic health institutions health centres and hospital will keep all the slides examined for mycobacterium tuberculosis. The regional reference laboratory will do external quality control check for five per cent of the laboratory results for all specimens.

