**Intervention sites**

The investigator, in collaboration with tuberculosis programme coordinators, will give training to health workers and community health agents about community based tuberculosis care and their role and responsibilities. The training will focus on tuberculosis case finding, case holding, drug management, recording and reporting as per the national guideline for community based tuberculosis prevention and control. The trainees will receive course materials and field guides to the trainees.

All diagnosed tuberculosis patients in the selected clusters will be included in the study. Health workers will inform tuberculosis patients about the disease and the selection criteria of treatment supervisors. Patients will select and come to health workers for discussion about treatment supervision. Once agreed upon, the health worker will discuss with treatment supervisor about community based tuberculosis care, their role and responsibility during the course of treatment.

Selection criteria for treatment supervisor selection is as follows: a volunteer leaving in the community who can read and write, can comprehend health education about tuberculosis prevention and control, has time to give daily dose as per the recommendation, can follow the patient through out the treatment duration and assist the patient during the follow up and drug collection. It is necessary that the treatment supervisors should have a known address so that supervisors from health facilities, Woreda, or investigator can contact during supervisory field visits in the course of patient management. Parents or guardians will supervise treatment of their children in paediatric age group less than 13 years if they can assume the role of treatment supervisor as per the selection criteria. If not, they will identify treatment supervisor.

Tuberculosis patients, who completed intensive phase in health facilities and patients on re-treatment regimen will not participate in the study. Treatment supervisors, who could not supervise at least the first two months of treatment, will be excluded.

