**Patient follow up and treatment outcome**

1. Disease classification PTB+ve ______ PTB -ve ______ EPTB ________

2. Patient category New____ Relapse____ Failure_____ Defaulter______

Transfer in____ other (specify) _________________

3. Sputum smear results of PTB +ve patients

2nd month __________ 5th month _________ 7th month _______

4. Treatment outcome cured ___ treatment completed ___ died ______

Defaulted ____ failure ____ transfer out _______

Other (specify) ___________________________

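### Study One cultures suspects' sputum, but the protocol states no route by which a positive culture in a microscopy-negative suspect reaches the treating health facility

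*Protocol*

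**What the plan says.** Study One, section 2.3, sets out the laboratory pathway. On who gives sputum it says: "All tuberculosis suspects who meet the criteria will give sputum specimen for laboratory examination". The specimens get Ziehl-Neelsen microscopy at the diagnostic facility. In addition, "laboratory technicians will send the sputum specimens to Yirgalem hospital for culture, bleach digestion technique and fluorescent microscopy", and on the culture method, "We will use Lowenstein-Jenson medium under standard culture requirement to grow mycobacterium tuberculosis". No sub-sampling is mentioned. The annexed form for the Yirgalem results has a culture column for each of the three specimens.

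Signed results go to an independent record keeper. The next step is: "The investigator will check the results and report those patients who turned out to be smear positive for tuberculosis". The treatment step follows directly: "Health workers will start them on antituberculosis treatment as per the national tuberculosis manual". Among the arrangements made in advance, those responsible "will set dates for sputum transporting, smear result, treatment and follow up of patients". That list names the smear result and does not name culture.

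Study Two, section 2.1 (Intervention sites), enters patients by diagnosis: "All diagnosed tuberculosis patients in the selected clusters will be included in the study". Its outcome form provides for "Disease classification PTB+ve ______ PTB -ve ______ EPTB".

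**The concern.** The study orders a culture, records it for each specimen and passes the results to the investigator. It then defines the patients to be reported by smear status. A suspect who is negative on all microscopy and positive on culture falls outside that definition, and no other sentence picks the result up.

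Two things are at stake. The first is the participant: a positive result for tuberculosis, produced by the study, could stay in its records. The Statement of the problem in Part One gives earlier treatment and less transmission as reasons for the work, so this outcome would run against the protocol's own purpose. The second is clarity between the studies. Study One runs alongside Study Two in the intervention clusters, and the protocol does not say whether a positive study culture makes a suspect a diagnosed patient for Study Two.

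**Working it through.** This is mainly a question of procedure, so the relevant sections are set side by side first.

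1. **Tests done.** Study One, section 2.3, lists Ziehl-Neelsen smear, fluorescent microscopy, bleach digestion and culture. Part One, section 6.2 (Study I), and Study One, section 2.1, repeat the culture step. Neither says where the culture result goes.
2. **Result released.** Section 2.3 has one release sentence, for smear-positive patients, and the treatment sentence that follows refers back to those patients.
3. **Timing.** The dates set in advance include one for the smear result and none for culture.
4. **Who falls outside.** The release sentence comes after the fluorescent and bleach examinations have been described, and both are microscopy methods. Smear positive may therefore include positives on either. The group that is certainly uncovered is culture-positive and negative on all microscopy.
5. **Study Two.** Entry covers all diagnosed patients. The stated patient exclusions are completion of the intensive phase in a facility and a re-treatment regimen. Smear-negative status is not an exclusion, and the outcome form has a class for it. Part One, section 6.2 (Study II), refers diagnosis to the national guideline.

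**The plan's own figure.** Study One, section 2.4, gives p = 0.20, d = 0.05 and z = 1.96. Then n = z² × p × (1 − p) / d² = 3.8416 × 0.16 / 0.0025 = 245.86, which rounds up to the stated 246. This figure is not in dispute.

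**Illustrative size.** 20% of 246 is 49.2. The documents give no sensitivity of smear against culture, so the values 50% and 80% below are assumptions.

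| Reading of the 20% | Formula for smear-negative, culture-positive | At 80% | At 50% |
| --- | --- | --- | --- |
| Smear-positive cases | 49.2 / s − 49.2 | 61.5 − 49.2 = 12.3 | 98.4 − 49.2 = 49.2 |
| All culture-positive cases | 49.2 × (1 − s) | 9.8 | 24.6 |

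Across both readings the range is about 10 to 49 suspects. It gives no credit for cases found by fluorescence or bleach microscopy, or by clinical diagnosis under the guideline. Any of these would lower the number left with culture as their only evidence.

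**The case against.** The best defence is that the protocol is silent here and forbids nothing. The release sentence does not say that smear-positive patients alone are reported. Section 2.3 also sets up a referral system between facilities, laboratory technicians and community health agents, and the national manual, which is not at hand, may govern the follow-up of smear-negative suspects. This stands in part: the text does not bar the return of a culture result. But the sentence is the stated rule for what follows the investigator's check. Staff who follow it have no instruction to send back a positive culture, and a general referral system does not say that a result held by the study's record keeper leaves the study.

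A reader might infer that culture-positive, smear-negative suspects are shut out of Study Two. The documents do not support that. Study Two takes all diagnosed patients and has a smear-negative class, so such a suspect enters if diagnosed by any other route. What can be said is that a patient whose only evidence is the unreported culture could be missed.

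A reader might also count every Ziehl-Neelsen-negative, culture-positive suspect as unreported, or assume that everyone interviewed is cultured. The first ignores the other microscopy methods. The second ignores that sputum is taken from suspects who meet the tool's criteria.

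The objection to the size also stands: the 20% is described as pulmonary cases detected by the zonal programme, not as smear-positive suspects, and the sensitivity is an outside assumption.

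Finally, simply registering culture-only cases in Study Two could do harm. Study One, section 2.1, places the screening study in intervention clusters, while control clusters keep conventional case finding with no study culture described. Patients found by culture alone would then be added to one arm only.

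**Conclusion.** The point holds in a limited form. Study One cultures the sputum of suspects who meet the tool's criteria, its one release rule covers smear-positive patients, and no section gives a route for a positive culture in a suspect negative on all microscopy. Followed as written, the procedure could leave a result that shows tuberculosis unreported to the treating facility.

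The number affected cannot be derived from the documents. The range of about 10 to 49 of 246 is an illustration that rests on the assumed 50% to 80% smear sensitivity and on the two readings of the 20%. No sample size, power or significance level changes. The change should be made because it concerns participants' own results and costs little.

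**What to change.** Amend the release sentence in Study One, section 2.3, so that positive culture results, like positive smears, are returned to the suspect's health facility when they become available, with the date of return recorded. Leave management to the national manual; no clinical rule is proposed here.

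Reconcile that section with Study Two, section 2.1 (Intervention sites), by stating whether a positive study culture counts as a diagnosis for Study Two. Because this culture is described only in intervention clusters, record the basis of diagnosis for each Study Two patient. Patients diagnosed by study culture alone can then be identified when the arms are compared.

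The cost is a reworded sentence, one further statement and one extra recorded item. No new test is needed. The small downside is tracing some suspects weeks after screening, once culture results arrive.
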